## Abstract

The diagnostic strategy for chronic thromboembolic pulmonary hypertension (CTEPH) is composed of two components required for a diagnosis of CTEPH: the presence of chronic pulmonary embolism and an elevated pulmonary artery pressure. The current guidelines require that ventilation–perfusion single-photon emission computed tomography (VQ-SPECT) is used for the first step diagnosis of chronic pulmonary embolism. However, VQ-SPECT exposes patients to ionizing radiation in a radiation sensitive population. The prospective, multicenter, comparative phase III diagnostic trial **C**TEP**H** di**agn**osis **E**urope - MRI (CHANGE-MRI, ClinicalTrials.gov identifier *NCT02791282*) aims to demonstrate whether functional lung MRI can serve as an equal rights alternative to VQ-SPECT in a diagnostic strategy for patients with suspected CTEPH. Positive findings are verified with catheter pulmonary angiography or computed tomography pulmonary angiography (gold standard). For comparing the imaging methods, a co-primary endpoint is used. (i) the proportion of patients with positive MRI in the group of patients who have a positive SPECT and gold standard diagnosis for chronic pulmonary embolism and (ii) the proportion of patients with positive MRI in the group of patients with negative SPECT and gold standard. The CHANGE-MRI trial will also investigate the performance of functional lung MRI without i.v. contrast agent as an index test and identify cardiac, hemodynamic, and pulmonary MRI-derived parameters to estimate pulmonary artery pressures and predict 6–12 month survival. Ultimately, this study will provide the necessary evidence for the discussion about changes in the recommendations on the diagnostic approach to CTEPH.

## Introduction

### The Clinical Problem

Chronic thromboembolic pulmonary hypertension (CTEPH) occurs in 0.1–4.0% of patients with acute pulmonary embolism (PE) within 2 years (1). If left untreated, the outlook for patients with CTEPH is dismal. Median survival is <2 years in patients who have a mean pulmonary artery pressure higher than 30 mm Hg at diagnosis (2). Right-heart failure is the most frequent cause of death. However, when treated successfully with endarterectomy, CTEPH patients have a good prognostic outcome (3), therefore timely diagnosis is of great importance. Advances in management have improved outcomes, but CTEPH remains a potentially fatal condition, especially when surgery is not an option (4, 5). The diagnostic approach according to the current guidelines for CTEPH starts with transthoracic echocardiography (6) to assess the likelihood of pulmonary hypertension, followed by ventilation-perfusion single-photon emission computed tomography (VQ-SPECT) to detect or rule out perfusion defects (7) (Figure 1). VQ-SPECT is currently the preferred imaging tool for screening because of its high sensitivity and a negative predictive value of virtually 100% (9).

**Figure 1 F1:**
[figure not shown]
Diagnostic algorithm for CTEPH based on the 2015 ESC/ERS Guidelines for the diagnosis and treatment of pulmonary hypertension with potential change in red (7, 8).

### The Need for a Trial

VQ-SPECT requires ionizing radiation, while MRI systems are not associated with any additional radiation dose and have increasing availability. Initially, a multicenter study conducted between 2006 and 2008 in 371 patients with suspected pulmonary embolism using Gadolinium-enhanced MR Angiography to detect pulmonary embolism showed a moderate test performance and modest patient compliance [PIOPED III (10)]. Meanwhile, novel 4D dynamic contrast-enhanced (DCE) lung perfusion magnetic resonance imaging (MRI) techniques (11) are widely available on current MRI systems and have shown excellent test performance in diagnosing CTEPH in a single center registry setting in Sheffield [ASPIRE registry (12)]. In addition, a non-contrast, free breathing ventilation perfusion MRI technique, known as the Fourier decomposition MRI method (13), has recently shown initial encouraging results in diagnosing chronic pulmonary embolism (14). In the CHANGE-MRI study we implemented phase-resolved functional lung (PREFUL) MRI as a secondary outcome parameter, which is a further development of Fourier Decomposition MRI depicting the whole breathing and cardiac cycle (15). These novel functional MRI techniques hold significant potential to be an equal rights non-ionizing alternative to VQ-SPECT in the near future, if they can demonstrate robust test performance in a prospective multicenter setting (Figure 2).

**Figure 2 F2:**
[figure not shown]
Cardio-pulmonary MRI **(A,B,D,E,F,H)** and V/Q SPECT **(C,G)** images of a patient with CTEPH. MRI angiography [coronal maximum intensity projection, **(A)**] Maximum intensity projection (MIP) depicts pulmonary artery stenosis and irregularities predominantly in the lower lobes as well as in the left upper lobe. Time resolved 4D MRI perfusion DCE angiography (coronal, acquisition time per volume: 1.3 s, voxel size 3 × 4 × 5 mm, **B**) depicts corresponding parenchymal hypoperfusion, which, matches with the Q-SPECT (coronal, voxel size 5 × 5 × 12 mm, **C**) findings. V-SPECT (coronal, voxel size 5 × 5 × 12 mm, **G**) shows relatively homogeneous ventilation. In accordance, neither infiltrates nor atelectasis are seen on T2 weighted Half-Fourier Acquisition Single-shot Turbo spin Echo (HASTE)-MRI (coronal, voxel size 2 × 2 × 6 mm, **F**), notice the signal in the main pulmonary arteries due to slow flow. V/Q Phase resolved functional lung MRI (PREFUL, coronal, voxel size 4 × 4 × 15 mm, **D,H**) depicts normal regional ventilation **(H)** and regions of hypoperfusion matching the V/Q SPECT **(C,G)** and DCE MRI **(B)** findings. Short axis cardiac cine MRI shows right ventricular hypertrophy and septal flattening (arrow) in systole due to increased pulmonary vascular resistance.

## Methods and Analysis

### Study Information

CHANGE-MRI is a prospective, multicenter, comparative phase III diagnostic study undertaken by the German Centre for Lung Research (DZL): Centre for Biomedical Research in Endstage and Obstructive Lung Disease Hannover (BREATH), the Universities of Giessen and Marburg Lung Centre (LGMLC), the Comprehensive Pneumology Centre Munich, the Translational Lung Research Centre Heidelberg (TLRC-H), the University of Sheffield, the Medical University of Vienna, the University Medical Centre of the Johannes Gutenberg University Mainz, the University Hospital Zurich and the University Hospital Regensburg. The study aims to demonstrate that functional lung MRI techniques can be an equal rights alternative to VQ-SPECT as a screening test in a diagnostic strategy for CTEPH where the positive findings of the screening test are verified with catheter pulmonary angiography or computed tomography pulmonary angiography (CPA/CTPA) in the diagnostic work-up.

Investigators from Hannover Medical School (MHH) designed the trial, and MHH acts as the study sponsor and is funded by the German Centre of Lung Research (DZL). A trial management group for the study comprises specialists from the disciplines of Pneumology, Nuclear Medicine, Radiology, Biostatistics, Medical Documentation and Medical Imaging and Computing. The study started recruitment in 2016. Ethical approval for the study was granted by MHH ethics committee (No 2678-2015). The trial is registered with ClinicalTrials.gov identifier *NCT02791282*.

### Objectives

The diagnostic strategy for CTEPH is basically composed of two components leading to a final diagnosis for or against CTEPH:

Presence of chronic pulmonary embolism, andPresence of elevated pulmonary artery pressure.

The tests to be compared in this study (MRI vs. SPECT) are diagnostic interventions for chronic pulmonary embolism (chronic PE). Diagnosis of elevated pulmonary artery pressure follows the routine clinical assessment with right heart catheterization. As such, the study primarily deals with the first step diagnosis of chronic pulmonary embolism. The medical hypothesis of the CHANGE-MRI trial is that the diagnostic performance of novel functional lung MRI is sufficient to be an equal rights alternative to VQ-SPECT—the current clinical standard—in the detection of chronic PE in the diagnostic algorithm for CTEPH and thus can reduce the radiation burden for patients. Therefore, the MRI should identify almost all correct cases in the SPECT—strategy and should not increase the rate of false positive findings

The study will be considered successful in demonstrating that MRI can replace SPECT if the following co-primary hypotheses can be confirmed for the interrelation of MRI and SPECT:

The probability that MRI is positive in patients who are SPECT positive and who have a positive gold standard is **larger than 95%** and,The probability that MRI is positive in patients who are SPECT negative and who have a negative gold standard is **smaller than 10%**.

To determine the sensitivity and specificity of functional MRI as co-primary endpoints of this diagnostic study, an alternative strategy would have been to send all study patients for a verification step with CPA/CTPA. However, this strategy was considered to imply an unacceptable increase in the diagnostic burden and radiation for patients who are not usually subjected to further diagnostic interventions.

Secondary objectives are:

- To demonstrate an additional benefit of MRI in comparison to SPECT with correct results of MRI (according to the gold standard) where SPECT showed false diagnoses- To compare the performance of SPECT and MRI using conventional diagnostic measures: sensitivity, specificity, positive and negative predictive value- to compare the performance of SPECT and MRI in subgroups of male and female and obese (BMI ≥ 28 kg/m^2^) and non-obese (BMI <28 kg/m^2^) patients- to evaluate the inter-rater reliability in SPECT assessment, MRI-assessment and CPA/CTPA assessment between local in-place read and blinded read- to compare SPECT and MRI regarding safety and procedure related limitations.

### Patients

The inclusion criteria are chosen to reflect exactly the clinical setting in the diagnostic algorithm for CTEPH. Here, MRI is positioned for an in-place validation compared to SPECT without any exclusion of subgroups compared to SPECT, except for inability to undergo MRI and pregnancy (see Table 1).

**Table 1 T1:** Patient inclusion and exclusion criteria.

Inclusion	• Transthoracic echocardiography suggests pulmonary hypertension
	• Patients with clinical suspicion for CTEPH, scheduled for SPECT
	• Provided informed consent for the study
	• Age >18 years
Exclusion	• Inability to undergo MRI (e.g., due to claustrophobia, cardiac pacemaker, hypersensitivity to MR i.v. contrast imaging agents)
	• Women who are pregnant or breast feeding

### Diagnostic Methods

#### Index Test

A robust functional cardio-pulmonary-MRI exam that can be conducted within 30 min without radiation burden is used as novel index test. In brief, the MRI protocol consists of anatomical MR sequences, to depict thoracic pathology (ECG gated steady state free precession sequences and Half-Fourier Acquisition Single-shot Turbo spin Echo imaging covering the whole thorax both in axial and coronal planes), coronal 2D Fast low Angle Shot stacked time series for 50 sec each covering the whole thorax and 2 additional sagittal 2D Fast low Angle Shot planes (one for each lung) in free breathing for PREFUL MRI, contrast enhanced pulmonary MRA (4D time resolved gradient echo MRA and 3D pulmonary MRA, total gadolinium dose 1.5 mmol/kg) as well as cardiac function (short axis cine stack and 4 chamber cine view). While retrospectively ECG gated cardiac cine sequences are used in the study protocol, novel fast real-time cardiac cine sequences (i.e., compressed sensing MRI techniques) may be used, especially in cases of arrhythmia or shortness of breath (16). For detailed description of the MRI protocol see Figure 3. A central read for cardiac function and strain analysis is performed using dedicated cardiac software (CMR42, Circle Cardiovascular Imaging). For the primary read all MRI data is available except PREFUL MRI. In a sub-study all MRI data is available except 4D time resolved gradient echo MRA and 3D pulmonary MRA to test PREFUL as a secondary outcome parameter without the need for i.v. contrast for CTEPH diagnosis.

**Figure 3 F3:**
[figure not shown]
Detailed description of the MRI protocol.

#### Reference Test

VQ-SPECT is used as the reference test in this study. In clinical practice, several CTEPH expert centers use perfusion single-photon emission computed tomography (Q-SPECT/CT) without concomitant ventilation SPECT (V-SPECT) to exclude or diagnose CTEPH, although not in compliance with the current ERS/ESC guidelines (8, 17). Therefore, in this study also Q-SPECT/CT is accepted as reference test, reflecting current clinical practice and real-world test performance. In this article, the reference test of VQ-SPECT or Q-SPECT/CT is termed SPECT. The duration of the intervention is ~60 min per patient. The radiation exposure applied by the reference test is ~1.2–2 mSv (17).

#### Diagnostic Gold Standard

Catheter pulmonary angiography or computed tomography pulmonary angiography (CPA/CTPA) is considered to be the current clinical gold standard for confirming chronic pulmonary embolism in a diagnostic algorithm (7). CTPA and CPA are well suited as verification step for the diagnosis of chronic pulmonary embolism (18). Nevertheless, they both have a considerable radiation burden on the patient. Therefore, in current diagnostic practice, in many expert centers only patients with a positive SPECT undergo a verification step with CPA/CTPA, whereas at some sites CPA/CTPA is used for verification of all patients. In this study, we only verify patients, if verification with CPA/CTPA is clinical routine at the respective study site. It is the responsibility of the treating pneumologist to decide whether verification by CPA/CTPA is clinically indicated. In any case, verification with CPA/CTPA is not part of study directives but a clinical decision.

A clinical follow-up after 6–12 months is implemented, where all patients are contacted and asked whether there has been any further intervention indicative (or contraindicative) of CTEPH, in order to identify cases diagnosed as false negative (or false positive, respectively) in the diagnostic work-up. Additionally, cases diagnosed as false negative by the screening test (SPECT negative patients are not verified by CPA/CTPA on a regular basis), but subsequently identified as positive can be captured by incorporation of the clinical follow up. Since the gold standard should capture the true diagnosis at inclusion, the clinical follow up diagnosis is restricted to be within 1 year of the inclusion to ensure that CTEPH—if diagnosed in the clinical follow up—was present at the inclusion already and did not develop afterwards.

With this trial design we avoid an increase in the diagnostic burden (i.e., the increased radiation of CPA/CTPA) for SPECT-negative patients without clinically indicated CPA/CTPA. A verification of all patients (to precisely estimate the sensitivity and specificity of functional MRI) was considered infeasible and ethically indefensible due to the application of the additional radiation dose required for CPA/CTPA without any clinical justification. Consequently, a composite gold standard for pulmonary embolism used in this trial combining SPECT, CPA/CTPA and follow-up. The composite gold standard is a diagnostic strategy with SPECT as screening test and CPA/CTPA as verification test, corrected by clinical diagnosis after 6–12 months:

If CPA/CTPA is performed during the initial diagnostic work-up, the gold standard is set to the result of CPA/CTPA corrected for the clinical diagnosis after 6–12 months. In cases of mismatch, the clinical 6–12 months follow-up diagnosis overrules the CPA/CTPA diagnosis (e.g., if CPA/CTPA diagnosis is negative but 6–12 months diagnosis is positive, the gold standard diagnosis is positive).If CPA/CTPA has not been conducted during initial diagnostic work-up, the gold standard is set to the clinical diagnosis after 6–12 months.

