## Discussion

In this study also Q-SPECT/CT is accepted as an approximation of the VQ-SPECT as reference test, reflecting current clinical practice and real-world test performance, although not in compliance with the current ESC/ERS guidelines (8, 17). This omission of V-SPECT will affect in particular specificity of the reference test in cases of Q-SPECT/CT, for CT cannot be regarded as a fully equivalent substitute for V SPECT.

For primary evaluation, the blinded reader assessment of SPECT and MRI are used to ensure the independency of the assessments and maximize internal validity. On the other hand, external validity of the results might be reduced by the standardized blinded assessment, which does not necessarily reproduce the clinical field of application completely. Consequently, for analyzing the external validity and generalizability of the results based on the primary blinded assessment, the in-place assessments of SPECT and MRI are used as secondary endpoints. While the independence of these assessments cannot be guaranteed, the clinical setting is well represented.

To avoid an increased radiation burden, in this trial the current gold-standard instrument CPA/CTPA is routinely only applied in SPECT-positive patients, which might induce differential verification bias (6, 19, 20). To mitigate this limitation, the follow-up information up to 1 year after study inclusion will be included into the final diagnosis of PE by correcting negative cases, which subsequently are identified as positive in the follow-up period or (although less probable) correcting positive cases, which subsequently are identified as negative.

Ethics votes from the Institutional Review Boards at all participating centers were obtained. The CHANGE-MRI study is designed so that no extra radiation in addition to the clinically indicated radiation-based imaging tests is applied to the study participants. Thus, approval by the Federal Office for radiation protection (Bundesamt für Strahlenschutz) was not required.

This study is conducted in compliance with the Declaration of Helsinki, ICH-E6-guidance, and for design issues regarding diagnostic validation studies, and the EMA Guideline on the Clinical Evaluation of Diagnostic Agents.

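### The follow-up question that can overrule CPA/CTPA concerns CTEPH, but the gold standard is meant to record chronic PE at inclusion, so angiographic chronic PE without CTEPH can become gold-standard negative

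*Protocol article*

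**What the plan says.** The Objectives section splits CTEPH into two components, chronic PE and elevated pulmonary artery pressure. It assigns MRI and SPECT to the first: "the study primarily deals with the first step diagnosis of chronic pulmonary embolism". The second is handled apart: "Diagnosis of elevated pulmonary artery pressure follows the routine clinical assessment with right heart catheterization".

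The Diagnostic Gold Standard section names CPA/CTPA as the accepted way to establish chronic PE, and it fixes the time point: "the gold standard should capture the true diagnosis at inclusion". At 6–12 months every patient is "asked whether there has been any further intervention indicative (or contraindicative) of CTEPH". The composite is introduced as a gold standard for pulmonary embolism and has two rules:

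- CPA/CTPA done at the initial work-up: its result stands unless follow-up differs. "In cases of mismatch, the clinical 6–12 months follow-up diagnosis overrules the CPA/CTPA diagnosis". The worked example goes from negative to positive: "if CPA/CTPA diagnosis is negative but 6–12 months diagnosis is positive, the gold standard diagnosis is positive".
- CPA/CTPA not done: the follow-up diagnosis is the whole gold standard.

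The reverse direction is also intended. The Diagnostic Gold Standard section says follow-up should identify false positives as well as false negatives, and the Discussion lists "although less probable) correcting positive cases, which subsequently are identified as negative".

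**The concern.** The overruling information concerns a disease with two components, and it replaces an angiographic finding about one of them. Chronic PE on CPA/CTPA with pressure that is not elevated is a true positive for the condition under study, yet it yields no CTEPH diagnosis. If the absence of that diagnosis at 6–12 months is treated as a mismatch, the patient becomes gold-standard negative.

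The one-year limit does not cover this case. Its stated purpose is to ensure that CTEPH found later was already there at inclusion, which justifies later positives only. The article gives no reason why a later negative shows that chronic PE seen on angiography was absent at inclusion.

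The gold standard defines the denominators of both co-primary endpoints as well as sensitivity, specificity and predictive values. A reclassified SPECT-positive patient leaves the first endpoint and enters the SPECT-positive, gold-negative cell, where a correct positive read counts as false. A reclassified SPECT-negative patient enters the second endpoint, where a correct positive MRI counts against MRI.

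**Working it through.** **Inputs.** Table 2(A), per 1,000 patients, MRI-positive of total:

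- SPECT+/gold+: 562 of 576
- SPECT−/gold+: 20 of 24
- SPECT+/gold−: 11 of 40
- SPECT−/gold−: 21 of 360

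Thresholds are 95% and 10%, one-sided alpha is 2.5% and N = 1080. The overrule rate is not given and is assumed below.

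**Reproducing the plan.** The one-sample formula is n = [1.96·√(p0(1−p0)) + 0.842·√(p1(1−p1))]² / (p1−p0)².

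- 0.95 against 0.98: 330.02, so 331. Total 331/0.58 = 571.
- 0.10 against 0.06: 387.96, so 388. Total 388/0.36 = 1077.8, stated as 1080.

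The planned sizes are sound. The issue is the definition of the gold standard.

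**Specificity (secondary), if 5% of SPECT+/gold+ patients are overruled to negative.** 0.05 × 576 ≈ 29 patients, of whom 29 × 14/576 ≈ 0.7 are MRI-negative.

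- SPECT: 360/400 = 90% becomes 360/429 = 83.9%.
- MRI: 368/400 = 92% becomes 368.7/429 = 85.9%.

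The gap between the tests stays at about 2 points.

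**Endpoint 1.** The denominator at N = 1080 is 576 × 1.08 = 622, falling to 622 × 0.95 = 591. The lower 95% Wilson limit exceeds 95% from 602 of 622, or 572 of 591. At a true proportion of 562/576 = 97.6%, exact binomial power is about 91% at both sizes. If overruled patients are MRI-positive as often as the rest, the proportion does not move. If they are MRI-positive less often, it is inflated. For example, take a true 95%, 5% overruled and 80% of those MRI-positive:

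- Apparent proportion: (0.95 − 0.05 × 0.80)/0.95 = 95.8%.
- Chance of declaring success (normal approximation, n = 591): about 12% instead of 2.5%.

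**Endpoint 2.** Let s of the 24 SPECT−/gold+ patients become negative, with 20/24 of them MRI-positive. The expected proportion is (21 + s·20/24)/(360 + s). With n = 388 the upper Wilson limit is below 10% for at most 27 MRI-positives, so power is P(X ≤ 27).

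| s of 24 | Proportion | Power, n = 388 |
|---|---|---|
| 0 | 21/360 = 5.8% | 85% |
| 1.2 (5%) | 22.0/361.2 = 6.1% | 80% |
| 5 (21%) | 25.2/365 = 6.9% | 57% |
| 10 (42%) | 29.3/370 = 7.9% | 28% |

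Letting the subgroup grow with the added patients (365 × 1.08 ≈ 394 for s = 5) gives 54% in that row and changes the others by about a point or less.

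**The case against.** **The target is stated as PE.** The composite is called a gold standard for pulmonary embolism, and the Discussion says follow-up feeds the final diagnosis of PE. An investigator could therefore apply the rule to PE alone. That is a fair reading, but the only described content of the follow-up contact is CTEPH. The article supports both readings, so the sections need reconciling. This is also not detail left to an unseen document: the overrule itself is stated in the article.

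**The case may be rare.** Inclusion requires echocardiography suggesting pulmonary hypertension and clinical suspicion of CTEPH, which should make chronic PE with normal pressure less common. The Discussion calls positive-to-negative corrections less probable. Both points limit the likely size, but neither stops the rule from operating.

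**Much of the endpoint 2 effect is not an overrule.** SPECT-negative patients are not routinely sent for CPA/CTPA, so for many the second rule applies and there is nothing to overrule. This stands. The article discloses differential verification bias, and restricting the overrule would not help these patients. Recording chronic PE separately would, where follow-up yields information on it.

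**The bias is conservative.** For endpoint 2 it works against MRI. For endpoint 1 it can work in favour of MRI if overruled patients are less often MRI-positive, so the direction is not assured.

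**A stronger reading.** A reader might infer that patients treated successfully before the contact become gold-standard negative. The article does not say so. A CTEPH-directed treatment is naturally an intervention indicative of CTEPH and would support a positive. The inference needs the follow-up diagnosis to mean current disease status, which the article nowhere states.

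**Conclusion.** The point holds as an inconsistency in a stated rule. The overrule runs in both directions, it draws on a CTEPH question, and it can cancel an angiographic finding of chronic PE without evidence that chronic PE was absent at inclusion.

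The size cannot be fixed from the article. At an assumed 5% rate in each cell, specificity falls by about 6 points for both tests, endpoint 1 keeps about 91% power, and endpoint 2 drops to about 80%, the planned level. A reader might take 28% as the expected power for endpoint 2. That figure requires 10 of 24 patients (42%) to be reclassified, and nothing in the article supports such a rate. It marks the far end of the range shown. Endpoint 2 is nevertheless the sensitive one, because it determines N and only 24 patients per 1,000 supply the shift.

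The change should be made, since the rule defines both co-primary denominators and correcting it needs no new imaging.

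**What to change.** 1. Reconcile the Objectives, Diagnostic Gold Standard and Discussion sections so that the follow-up diagnosis entering the gold standard is chronic PE status at inclusion. Record it as an item separate from CTEPH. This covers patients with and without CPA/CTPA.
2. Let follow-up reverse a positive CPA/CTPA for the gold standard only on evidence that chronic PE was absent at inclusion. Absence of pulmonary hypertension alone does not qualify.
3. Report how many patients were reclassified in each direction, by SPECT result.
4. Add a sensitivity analysis of both co-primary endpoints that uses the CPA/CTPA result without positive-to-negative overrules.

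The cost is one rule change, one follow-up item (or recoding from existing clinical records) and slightly more work per overruled case. No extra imaging or radiation is involved.
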